### *Statistical analyses*

Prior to breaking the treatment code at the end of the study, all decisions on the evaluability of data from each individual patient for the statistical analyses are made and documented. The effects of treatment will be analysed according to treatment group. Primary analyses will be comparing changes in cell counts per treatment group in time. Secondary analyses will compare changes in clinical outcome variables such as lung function and respiratory symptoms with changes in cell counts.

Linear mixed effects models will be used to estimate the effects of treatment on changes in primary outcome variables (cell counts) and the secondary outcome variables (such as lung function, bronchial hyperresponsiveness, number of blood eosinophil count). Graphical visual inspection will be used to determine which model has the best fit (linear/non-linear model). Descriptive statistics will be presented by visit. Confidence intervals will be computed using a 95% confidence interval level and p-values <0.05 are considered to be statistically significant.

In addition, the baseline values of lung function, bronchial biopsy, bronchoalveolar lavage and sputum induction will be evaluated as possible explanatory variables for the outcome. Smoking habits will be evaluated as the duration of smoking (years), average daily consumption prior to the study, average daily consumption during the periods between visits, previous cigarette consumption expressed as packyears.

Time points will be calculated as time elapsed since baseline visit.

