## **Outcome parameters**

### Primary

#### Inflammation

- localisation, numbers and profile of neutrophils, eosinophils, macrophages, and CD8+ T cells in bronchial biopsy specimens

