## Study design

In this prospective, longitudinal, double blind study COPD patients will be followed up for 2.5 years (see *figure*). The study begins as a 3 groups parallel design during 6 months, followed by a 4 groups parallel design during 24 months. The aim is to finish the study with 50 patients in each of the 4 parallel groups at 30 months.

Patients will be treated by the investigator-physician with inhaled corticosteroids (500 µg b.i.d. fluticasone by DiscusR), or inhaled corticosteroids with long-acting  $\beta_2$ -agonist (+ 50 µg b.i.d. salmeterol), or a matching placebo for the first 6 months. Thereafter, half of the corticosteroid group will continue and the other half will receive placebo for 2 years. The patients who will be treated with placebo or inhaled corticosteroids + salmeterol continue their treatment during the complete period of 2.5 years. Rescue treatment will be on demand usage of inhaled inpratropium bromide, which is a standard bronchodilator in COPD [Siafakas 1995].

Subjects who fulfil all inclusion criteria and none of the exclusion criteria (see patient selection) will be allocated to receive placebo, inhaled corticosteroids (equivalents of 500 µg b.i.d. = 1000 µg fluticasone) or inhaled corticosteroids + salmeterol at the beginning of the study using the minimization method. The use of minimization will provide treatment groups that are closely balanced for a number of variables (centre, gender, current smoker, FEV1/IVC < 60%, PC20 methacholine < 2 mg/ml), which might influence the primary and secondary outcome variables [Altman 1995]. The first patient is given a treatment at random. For each subsequent patient we will determine which treatment will lead to better balance between the groups with respect to centre, gender, smoking, FEV1/IVC and PC20. The group with inhaled steroid will be randomly allocated to either the steroid group or the placebo group after 6 months of steroid treatment. Minimization will be performed using a computerized method [Pocock 1983].

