## Measurements

Measurements of symptoms, QOL, and spirometry (postbronchodilator) will be made every 3 months. In addition, exhaled nitric oxide (NO), bodyplethysmography and carbon-monoxide diffusion capacity will be measured at 0, 6 and 30 months. Bronchial biopsies, bronchoalveolar lavage, and sputum induction will also be performed at 0, 6 and 30 months. Peripheral blood eosinophils, IgE, and PC20 methacholine at 0, 6 and 30 months. In bronchial biopsies,

bronchoalveolar lavage and sputum special attention will be paid to the number of lymphocytes, neutrophils, eosinophils, macrophages, mast cells, and the state of activation of these cells and the epithelium.

Once during the study a spiral computed tomography (CT-scan) will be performed to quantify the presence of pulmonary emphysema in each patient [Gevenois 1996], and EDTA-anti-coagulated whole blood will be collected for DNA-isolation, for future studies on gene polymorphisms possibly associated with glucocorticoid responsiveness or other study outcomes.

The effects of treatment will be analysed by relating the observed changes in clinical and pathophysiological outcome, to those in cellular and histological outcome (see analysis).

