### *Quantitative assessments in bronchial biopsies*

All biopsy specimens will be coded and sections will be examined by a single investigator in a blinded fashion, by means of a semi-automated image analysis system using a 200x magnification. Images of areas with well preserved tissue structure and without bronchus associated lymphoid tissue will serve as basis for further computer-aided analysis. For subepithelial analysis, the widest possible zone of maximal 125  $\mu\text{m}$  deep beneath the epithelial basement membrane will be delineated excluding damaged tissue, mucus-secreting glands, and airway smooth muscle (Sont 1996, 1997; Grashoff, 1997; Ten Hacken 1997, 1998). For epithelial analysis, the epithelium will be regarded using the same criteria (Grashoff, 1997). The number of positively staining nucleated inflammatory cells will be counted by a validated full automated procedure (Sont 1998) within the largest possible area per biopsy section (minimally 20,000  $\mu\text{m}^2$ ), and expressed as the number of cells / 0.1  $\text{mm}^2$  (subepithelial) or per 0.1  $\text{mm}^2$  and per mm basement membrane (epithelial). Expression of cytokines and SLPI in the airway epithelium and lamina propria will be semi-quantitatively scored (Sont 1997; de Boer 1998) and quantitatively assessed by densitometric analysis using a digital image analysis system.

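### Four unranked primary cell counts share a flat p<0.05 rule in a trial sized for one count and one contrast, so the primary false-positive risk exceeds 5%, by an amount the protocol leaves open

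*Protocol*

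**What the plan says.** Outcome parameters, Primary, lists "localisation, numbers and profile of neutrophils, eosinophils, macrophages, and CD8"-positive T cells in bronchial biopsies. No cell type comes before another.

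Quantitative assessments in bronchial biopsies describes two compartments: "For subepithelial analysis, the widest possible zone of maximal 125" micrometres deep, and then "For epithelial analysis, the epithelium will be regarded using the same criteria". Epithelial counts are expressed both per area and per length of basement membrane.

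Measurements sets the biopsy times: "Bronchial biopsies, bronchoalveolar lavage, and sputum induction will also be performed at 0, 6 and 30 months". Study design sets the groups: "The study begins as a 3 groups parallel design during 6 months, followed by a 4 groups parallel design during 24 months".

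Statistical analyses defines the primary comparison only as follows: "Primary analyses will be comparing changes in cell counts per treatment group in time". It names linear mixed effects models and then gives one rule for all outcomes: "Confidence intervals will be computed using a 95% confidence interval level and p-values <0.05 are considered to be statistically significant".

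Determination of the sample size works with a single cell type at alpha 0.05 and power 0.80. With 50 per arm and an SD of 2.34-fold, it gives a detectable ratio of 1.62 between two groups.

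**The concern.** The primary outcome has several parts, and any one of them can yield a significant result at the full 0.05. No main cell type, compartment, contrast or visit is fixed in the analysis section, and there is no testing order or adjustment. A primary effect could then be reported for whichever cell type and comparison happened to fall below 0.05, with a false-positive risk well above the nominal level.

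The sample size carries the same gap. It is correct for one test but does not describe the power of a primary analysis that controls error over four cell types.

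**Working it through.** **Inputs from the protocol.** Four primary cell types; two compartments; post-baseline biopsies at months 6 and 30; three groups to month 6 and four to month 30; threshold 0.05; SD 2.34-fold (ln 2.34 = 0.850); 50 per arm; power 0.80.

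**Assumptions.** Tests are two-sided, as the 95% intervals suggest. Power of 0.80 is stated for the within-group calculation and is taken to carry over to the 1.62 figure. At month 6 the two fluticasone-alone arms are pooled (100). The correlation between cell types is not given, so a range of 0 to 0.7 is used.

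**Step 1: reproduce the protocol's figure.** The detectable ratio is exp[(z for alpha + z for power) × ln 2.34 × √(1/n1 + 1/n2)].
- Normal approximation: exp[(1.960 + 0.842) × 0.850 × √(2/50)] = exp(0.476) = 1.61.
- Noncentral t with 98 degrees of freedom: 1.618, that is 1.62.

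The stated figure therefore rests on an unadjusted 0.05 for one count and one pair of groups.

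**Step 2: error for independent tests.** The chance of at least one false positive in m tests is 1 − 0.95^m.
- m = 4: 0.186
- m = 12 (four cell types, three placebo contrasts): 0.460
- m = 24 (four cell types, six pairs): 0.708

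Contrasts that share an arm are correlated, so the last two are too high and simulation is needed.

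**Step 3: simulation under no effect anywhere.** Four cell types, one compartment, one visit:

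| Reading of the plan | Correlation 0 | Correlation 0.7 |
|---|---|---|
| One omnibus test per cell type | 18% | 13% |
| Month 6, two contrasts with placebo | 31% | 22% |
| Month 6, all three pairs | 40% | 29% |
| Month 30, three contrasts with placebo | 42% | 30% |
| Month 30, all six pairs | 60% | 45% |

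Counting both compartments raises the month-30 figures to 66% to 41% for contrasts with placebo, and 84% to 56% for all pairs (correlation between compartments 0 to 0.8).

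**Step 4: detectable ratio at alpha 0.0125.** The quantile is 2.498, and 2.498 + 0.842 = 3.340.
- 50 v 50: exp(3.340 × 0.850 × 0.200) = 1.76 by the normal approximation; 1.78 by noncentral t, against 1.62 unadjusted.
- 100 v 50: √(1/100 + 1/50) = 0.173. Noncentral t gives 1.64, against 1.51 unadjusted.
- Power for a 1.62-fold ratio at 50 v 50: ln 1.62 / (0.850 × 0.200) = 2.84, and Φ(2.84 − 2.498) = 0.63 by the normal approximation, down from 0.81.

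**The case against.** Four objections deserve weight.

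**The tests are not listed.** Statistical analyses gives a threshold and a model class. A reader might infer that every cell type, compartment, contrast and visit is tested separately, but the text does not say so, and one omnibus test per cell type fits it equally well. This stands, and it is why the size is given by reading.

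**The larger figures are conditional.** A reader might infer a 45% to 60% risk at any single visit, or that a false primary finding is more likely than not. The documents support neither. The 45% to 60% range needs all six pairs, which exist only at month 30. Every one-compartment figure for month 6, and every one-compartment figure for contrasts with placebo at a single visit, is below 50%. For two visits, 68% to 83% results only if six contrasts are counted at month 6, where three groups allow three. With three and then six contrasts, and the same assumed between-visit correlation of 0.3, the range is 60% to 75%.

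**The hypotheses limit the choice.** Hypothesis predicts an early reduction in inflammation, sets six months of treatment against continuation, and expects no pathological change from adding salmeterol. Aim says these are to be tested. That narrows the plausible contrasts, but it ranks no cell type or compartment and is not carried into the analysis section.

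**An analysis plan may settle it.** Multiplicity is often handled in a statistical analysis plan, and one may exist. A reader might infer that the trial cannot confirm any primary result; that cannot be said without seeing it. Still, the protocol does not merely stay silent. It fixes a flat 0.05 rule and a sample size built on it, and an adjusting plan would depart from both.

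It is also fair that this is a mechanistic biopsy study, where the degree of adjustment across distinct cell types is partly a matter of judgement. That bears on severity more than on substance.

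**Conclusion.** The point holds in conditional form. The protocol fixes several unranked primary counts, a flat 0.05 rule, and a sample size for one count and one contrast. Even the mildest reading worked here gives 13% to 18%, more than twice the nominal 5%. The most extensive one-compartment, single-visit reading, all pairs at month 30, gives 45% to 60%. Which applies cannot be settled from the protocol.

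These figures assume no true effects, two-sided tests and equal correlation of 0 to 0.7 between cell types. A rule requiring all four cell types to be significant would keep the error at or below 5%, but the protocol states no such rule.

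This should be fixed. It does not invalidate the design.

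**What to change.** In Outcome parameters and Statistical analyses, name as primary the subepithelial counts per 0.1 mm² of the four cell types. Give each cell type alpha 0.05/4 = 0.0125 and, within it, test in fixed order:

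1. Pooled fluticasone alone v placebo, change from baseline to month 6.
2. Only if step 1 is significant for that cell type: 6-month v 30-month fluticasone, change from month 6 to month 30.

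These contrasts follow the first two hypotheses. A fixed order within a cell type holds its error at 0.0125, and four cell types sum to at most 0.05 whatever their correlation. The gate for each cell type matters. With Holm at the full 0.05 in each step, and step 2 opened by any single success, the simulated family-wise error reaches about 9.6% (one cell type truly affected at step 1, no effect at step 2).

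Report epithelial counts, cell profile and all other contrasts as secondary, with 95% intervals and no confirmatory claim.

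The change is to wording, but it has a price in sensitivity. At 80% power the detectable ratio is 1.64 instead of 1.51 at step 1 (100 v 50) and 1.78 instead of 1.62 at step 2 (50 v 50). Both stay below the twofold difference used elsewhere in the sample-size section. They assume that the 2.34-fold SD applies to both changes. Determination of the sample size should restate them.

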# VRAGENLIJST

## BRONCHOSCOPISCH ONDERZOEK

[figure not shown]

Groningen  
Leiden  
Universities  
Corticosteroids in  
Obstructive  
Lung  
Disease

Zoals afgesproken is hier de vragenlijst over de bronchoscopie. Deze vragenlijst vormt voor u de basis om verder mee te doen aan het wetenschappelijk onderzoek naar de behandeling van patiënten met COPD. Na het invullen kunt u rustig nadenken over verdere deelname aan de studie. Wij zullen contact met u opnemen en u kunt dan met ons bespreken welke beslissing u heeft genomen. Indien u deel wilt nemen aan het vervolg van het onderzoek zullen wij u vragen nogmaals een algemeen toestemmingsformulier te ondertekenen.

Wilt u de onderstaande vragen beantwoorden door een kruisje te zetten in één van de vakjes, waarmee u aangeeft of u het al dan niet met deze stelling eens bent. Na het invullen kunt u de vragenlijst in de bijgevoegde retourenvelop voegen en op de bus doen.

### Voorbeeld:

|                                      |                           |                                                   |                      |
|--------------------------------------|---------------------------|---------------------------------------------------|----------------------|
| 0. Het was vandaag mooi weer.        | helemaal
niet mee eens | -3 -2 -1 0 1 2 3
 --- --- --- --- --- --- ---X | helemaal
mee eens |
| Hopelijk was dit een juist antwoord! |                           |                                                   |                      |

### Vragenlijst:

|                                                                             |                           |                                                  |                      |
|-----------------------------------------------------------------------------|---------------------------|--------------------------------------------------|----------------------|
| 1 Ik vind een bronchoscopie een belastend onderzoek.                        | helemaal
niet mee eens | -3 -2 -1 0 1 2 3
 --- --- --- --- --- --- --- | helemaal
mee eens |
| 2 Een bronchoscopie vind ik meer belastend dan de inhalatie-provokatietest. | helemaal
niet mee eens | -3 -2 -1 0 1 2 3
 --- --- --- --- --- --- --- | helemaal
mee eens |
| 3 Ieder ander zou ik een bronchoscopie afraden.                             | helemaal
niet mee eens | -3 -2 -1 0 1 2 3
 --- --- --- --- --- --- --- | helemaal
mee eens |
| 4 Ik heb veel moeten hoesten tijdens de bronchoscopie.                      | helemaal
niet mee eens | -3 -2 -1 0 1 2 3
 --- --- --- --- --- --- --- | helemaal
mee eens |
| 5 Ik heb erg tegen de bronchoscopie opgezien.                               | helemaal
niet mee eens | -3 -2 -1 0 1 2 3
 --- --- --- --- --- --- --- | helemaal
mee eens |
| 6 Ik was erg kortademig tijdens de bronchoscopie.                           | helemaal
niet mee eens | -3 -2 -1 0 1 2 3
 --- --- --- --- --- --- --- | helemaal
mee eens |
| 7 Ik wist van tevoren precies hoe de bronchoscopie zou verlopen.            | helemaal
niet mee eens | -3 -2 -1 0 1 2 3
 --- --- --- --- --- --- --- | helemaal
mee eens |

|                                     |                           |                                              |                      |
|-------------------------------------|---------------------------|----------------------------------------------|----------------------|
| 8. Dit was een vervelend onderzoek. | helemaal
niet mee eens | -3 -2 -1 0 1 2 3
 --- --- --- --- --- --- | helemaal
mee eens |
|-------------------------------------|---------------------------|----------------------------------------------|----------------------|

|                                                           |                           |                                              |                      |
|-----------------------------------------------------------|---------------------------|----------------------------------------------|----------------------|
| 9. Een volgende keer zou ik deze bronchoscopie weer doen. | helemaal
niet mee eens | -3 -2 -1 0 1 2 3
 --- --- --- --- --- --- | helemaal
mee eens |
|-----------------------------------------------------------|---------------------------|----------------------------------------------|----------------------|

|                                                                               |                           |                                              |                      |
|-------------------------------------------------------------------------------|---------------------------|----------------------------------------------|----------------------|
| 10. De rest van de dag heb ik weinig hinder van de bronchoscopie ondervonden. | helemaal
niet mee eens | -3 -2 -1 0 1 2 3
 --- --- --- --- --- --- | helemaal
mee eens |
|-------------------------------------------------------------------------------|---------------------------|----------------------------------------------|----------------------|

Tenslotte willen we u nog een paar vragen stellen over het beloop van de bronchoscopie, om zonodig dingen te verbeteren:

|                                             |                           |                                              |                      |
|---------------------------------------------|---------------------------|----------------------------------------------|----------------------|
| 11. Ik vond de informatie vooraf duidelijk. | helemaal
niet mee eens | -3 -2 -1 0 1 2 3
 --- --- --- --- --- --- | helemaal
mee eens |
|---------------------------------------------|---------------------------|----------------------------------------------|----------------------|

|                                                  |                           |                                              |                      |
|--------------------------------------------------|---------------------------|----------------------------------------------|----------------------|
| 12. Het bekijken van de video vooraf was nuttig. | helemaal
niet mee eens | -3 -2 -1 0 1 2 3
 --- --- --- --- --- --- | helemaal
mee eens |
|--------------------------------------------------|---------------------------|----------------------------------------------|----------------------|

|                                                                             |                           |                                              |                      |
|-----------------------------------------------------------------------------|---------------------------|----------------------------------------------|----------------------|
| 13. Met de verkregen informatie was ik goed op de bronchoscopie voorbereid. | helemaal
niet mee eens | -3 -2 -1 0 1 2 3
 --- --- --- --- --- --- | helemaal
mee eens |
|-----------------------------------------------------------------------------|---------------------------|----------------------------------------------|----------------------|

|                                                           |                           |                                              |                      |
|-----------------------------------------------------------|---------------------------|----------------------------------------------|----------------------|
| 14. Ik vond de begeleiding tijdens de bronchoscopie goed. | helemaal
niet mee eens | -3 -2 -1 0 1 2 3
 --- --- --- --- --- --- | helemaal
mee eens |
|-----------------------------------------------------------|---------------------------|----------------------------------------------|----------------------|

|                                          |               |                         |          |
|------------------------------------------|---------------|-------------------------|----------|
| 15. De nazorg na het onderzoek was goed. | helemaal      | -3 -2 -1 0 1 2 3        | helemaal |
|                                          | niet mee eens | --- --- --- --- --- --- | mee eens |

17. Wat vond u het vervelendste onderdeel van de bronchoscopie?

18. Heeft u nog opmerkingen of suggesties betreffende de bronchoscopie?
